### Study methods and procedures

Eligible children will be identified by the nurse and clinician on duty and registered in the eligibility screening log. A member of the trial team will then perform a rapid structured assessment of heart rate, oxygen saturation (pulse oximetry), respiratory rate, axillary temperature, blood pressure, markers of shock (capillary refill time, pulse volume and assessment of lower limb temperature) and severity (conscious level and respiratory distress). Children who are potentially eligible with suspected severe malaria will have a rapid bedside malaria test (detecting
*P. falciparum* histidine-rich protein 2, HRP2) to determine malaria status and eligibility.

### Randomisation procedure

Randomisation lists will be generated and kept at the Medical Research Council (MRC) Clinical Trials Unit at University College London, London. The randomisation envelopes will be prepared before the trial, using the lists at the Clinical Trials Facilty, KEMRI Wellcome Trust Research Programme (KWTRP), Kilifi, Kenya. These will be opaque and sealed and will contain a card with allocation. Children will be randomised (1:1:1) to receive 10, 15 or 20 mg/kg azithromycin (based on weight-bands). The cards will be numbered consecutively and opened in numerical order. Clinicians will be aware of the treatment-group dose assignments, but the laboratory tests are to be performed in a blinded manner.

### Consent process

Once eligibility has been confirmed, authorised trial staff will approach parents/guardians to invite their child to take part in the trial. An information sheet will be provided to the parent/guardian in their usual language containing details of the TABS trial. The sheet will be read aloud to those who are unable to read. The doctor/nurse will check that the information has been fully understood and parents/guardians will be encouraged to ask questions they may have about their child’s participation in TABS trial. The information sheet and consent includes details of the clinical trial, follow up and additional biological samples taken for the trial and permissions for sample storage. Where possible, prospective written informed consent will be sought from parents/guardians who will then be asked to sign the consent form. Consent will include permission for the collection of admission and follow-up blood samples for later aetiological investigations. If parents/guardians are unable to sign, a thumbprint will be taken in lieu of a signature. A copy of the consent form will be given to the parent/guardian, the original placed in the patient’s medical notes, and a copy kept in the investigator site file. A number of children will present as emergencies where delay in study enrolment, and thus treatment, will not be practical or indeed humane. We will use a modified form of deferred consent; used in the FEAST trial
^
22
^ and for which we have received ethical approval. It proposes to use a ‘two-stage’ consent process in this circumstance
^
26
^. Verbal assent will be sought from parents or guardians by the admitting medical team if it is considered that the full consent process would significantly delay treatment allocation, and consequently could be detrimental to the child’s health. Full consent will be sought once the child’s clinical condition has been stabilized. Caregivers will be provided with a brief verbal description of the trial and will be given the opportunity to “opt out”. As in the FEAST trial, if following an assent process a child died prior to full written consent, full consent would not be sought. This process of emergency consent was approved for FEAST and has been subsequently approved for use in a TRACT transfusion trial in Uganda and Blantyre
^
23
^.

### Treatment allocation

Following consent, children will be randomly allocated to the treatment arms. Children, on admission to hospital with severe malaria (
*see Inclusion criteria above*) eligible for the trial will be randomised to one of three doses of adjunctive once daily oral azithromycin doses, which will be given for five days in addition to a three-day course of parenteral artesunate.
The comparator cohort with non-severe malaria will receive usual standard of care (oral artemisinin combination therapy). See Study Flow (
Figure 1).

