### Target population

Current recommendations indicate that antibiotics should be given to ‘all children with suspected severe malaria in areas of moderate and high transmission until a bacterial infection is excluded’
^
10
^. However, WHO definitions of severe malaria are very broad, incorporating high parasitaemia as a single criterion, and are thus applicable to a large proportion of paediatric admissions in such regions, with a relatively overall low case fatality (1–2%)
^
20
^, who are unlikely to benefit from antimicrobial therapy as a group. For this study (and in a future trial) we aim to target antibiotics to children with the highest risk of bacterial co-infection, meeting ‘Teule’ criteria
^
11
^: that is, with malaria (positive blood film or ParacheckTM rapid diagnostic test, RDT); temperature > 38°C or < 36°C; and ≥1 of prostration, respiratory distress, haemoglobin (Hb) <5g/dl or HIV. These criteria identified 85% of bacterial co-infections, with a three-fold higher mortality than children admitted with malaria without these criteria.

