### Credibility: can antibiotics be targeted?

A major legitimate concern is whether future management guidelines can be implemented which try to reduce the overuse of antibiotics where microbiology services are poor or non-existent, thus an approach to targeting only those with IBI is not feasible in much of Africa. Within the context of this study and to inform a future trial, we aim to investigate approaches (that may be generalizable in future) to targeting antibiotics. We propose to use (i) simple clinical criteria: proposed by Nadjm
*et al.*
^
11
^, the Teule criteria identifies 85% of malaria cases with culture-proven bacteraemia: a pathogen was isolated from 20% children meeting these criteria. Simple and objective criteria identifying those at risk would be more generalizable outside research centres and would be validated in this study. (ii) Potential biomarkers: even when quality-controlled blood-culture facilities are available, low sensitivity (due to frequent pre-hospital antibiotic therapy, low culture volumes from children and low bacterial density) and long times to culture-positivity (typically two-three days) mean that alternative approaches for identifying concurrent gram-negative bacteraemia would be highly valuable.

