### Specific objectives

(i)   To conduct a Phase I/II trial comparing three doses of azithromycin: 10, 15 and 20 mg/kg (prescribed for feasibility by weight-bands) spanning the lowest to highest mg/kg doses demonstrated to be equally effective as parenteral treatment for other salmonellae infection.

(ii)   To determine, via PKPD modelling, the optimal azithromycin dose in severe malaria, and investigate associations between azithromycin exposure and pathogen susceptibility (minimum inhibitory concentration, MIC) with treatment outcome. Outcome measures will consist of changes in C-reactive protein (CRP), a putative marker of sepsis at 72 hours (continuous) and microbiological cure (seven-day) (binary), alone and as a composite with seven-day survival, while providing preliminary data on longer-term survival (to day 90).

(iii)   To evaluate whether a combination of clinical, point-of-care diagnostic tests, and/or biomarkers can accurately identify the sub-group of severe malaria with culture-proven bacteraemia by comparison with a control cohort of children hospitalized with severe malaria but not meeting Teule criteria, at low risk of bacterial co-infection.

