### Controls

The control cohort of children (n=50) are those hospitalised with severe malaria but not meeting Teule criteria (i.e., low risk of bacterial co-infection) whose parents are willing/able to provide consent.

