### Exclusion criteria (cases only)

Major contraindications to azithromycin, e.g. strong existing clinical diagnosis of QT-prolongation. Concomitant use of interacting drugs: drugs that may cause QT-prolongation or drugs that may cause a pharmacokinetic interaction with azithromycin, like strong CYP3A/P-GP inducers and concomitantly administered antacids. 

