## Sampling

### Sample size determination

A formal sample size was not calculated. Phase I/II trials are an important step in the assessment of new or existing interventions providing the first data on the feasibility of using a product in a new application. They assess the effect of products (how well they work), and the side effects they may have. They are not usually designed to compare superiority of different products or interventions.

The aim is to generate pilot efficacy data on the optimal azithromycin dose for children with severe malaria, which will inform the design of a later larger Phase III trial. The numbers required to address the trial objectives are therefore balanced against the exposure of children in these settings to a therapeutic intervention (dose) for which there are limited data to date.

The overall sample size for the trial will be 105 children randomised 1:1:1 to receive 10, 15 or 20mg/kg azithromycin (based on weight-bands). This is sufficient for the PKPD sampling and modelling to determine an optimal dose in children with severe malaria using change in CRP at 72 hours, and microbiological cure (seven-day) alone and with seven-day survival. This is under the assumption that 20% of enrolled children (meeting Teule severity criteria) will have bacteraemia and that 80% of these infections will be caused by NTS or other enteric gram-negative organisms based on previous research. 

Based on Monte Carlo simulations, we expect that all dose groups should reach the population reference target (adult) AUC24h of at least 3.4 h*mg/L
^
24
^, although there are no data on absorption in severe malaria, which is characterised by impaired gut function
^
25
^, hence the need for this pilot. Along with the 105 children with Teule criteria we will enrol 50 children meeting other inclusion criteria but without Teule criteria (and without any exclusion criteria) into the control group.

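### The control cohort is defined inconsistently on severity, temperature and exclusions, so the population behind the bacteraemia-targeting result is unclear

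*Protocol article*

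**What the plan says.** The control cohort exists for the second principal objective. Specific objectives (iii) asks whether clinical signs, point-of-care tests or biomarkers can "accurately identify the sub-group of severe malaria with culture-proven bacteraemia by comparison with a control cohort of children hospitalized with severe malaria". Hypothesis 2 is framed in the same way.

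The protocol article describes who the controls are in several places:

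- **Controls:** "The control cohort of children (n=50) are those hospitalised with severe malaria but not meeting Teule criteria". Hypothesis 2, Specific objectives (iii), Biomarker and gut barrier function, and the Discussion agree with this.
- **Treatment allocation:** "The comparator cohort with non-severe malaria will receive usual standard of care (oral artemisinin combination therapy".
- **Sample size determination:** "we will enrol 50 children meeting other inclusion criteria but without Teule criteria (and without any exclusion criteria) into the control group". No severity requirement is named.
- **Exclusion criteria:** the heading itself reads "Exclusion criteria (cases only".

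The Teule criteria also appear in two forms. Target population gives them, in a child with malaria, as "temperature > 38°C or < 36°C; and ≥1 of prostration, respiratory distress, haemoglobin (Hb) <5g/dl or HIV", so temperature is a component. The Inclusion criteria for cases list abnormal axillary temperature as item i and the Teule severity criteria, with only the four signs, as item ii.

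**The concern.** Severe and non-severe malaria cannot both describe the same 50 children. The Treatment allocation sentence is current text. It attaches a treatment statement to the milder description and contrasts it with the parenteral regimen of the cases, so it reads as a coherent account of a different cohort. A reader cannot tell from the article which children were to be enrolled.

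The consequence is more than clerical. CRP, procalcitonin and endotoxin may be higher in sicker children whether or not they are bacteraemic. If the controls are milder than the cases, a marker can look specific for bacteraemia when part of what it detects is severity. The targeting result is meant to inform the strata of a Phase III trial in severe malaria, so both the population it applies to and its apparent accuracy depend on this definition.

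**Working it through.** **Step 1. The definitions side by side**

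| Section | Severity | Exclusions applied to controls |
|---|---|---|
| Controls (and four sections that agree on severity) | severe | not stated |
| Treatment allocation | non-severe | not stated |
| Sample size determination | not stated | yes |
| Exclusion criteria heading | not stated | no, cases only |

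The first two rows exclude each other on severity. The last two exclude each other on exclusions. The Sample size wording can overlap with either severity description, so it does not settle which is meant.

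**Step 2. Temperature**

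Take a normothermic child with one severity sign, such as prostration, and hold each form of Teule fixed:

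- *Target population form (temperature inside Teule).* The child does not meet Teule. The other inclusion criteria are then age, *P. falciparum* malaria and consent. The child can be a control under both the Controls and the Sample size sections, provided the malaria counts as severe.
- *Inclusion criteria form (temperature separate).* The child meets the Teule severity item and cannot be a control under either section. The other inclusion criteria now include abnormal temperature, so the Sample size section would require controls to be febrile or hypothermic.

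The ambiguity therefore lies between Target population and Inclusion criteria.

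**Step 3. How much of the comparator group the controls supply**

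Inputs from the article:

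- 105 cases and 50 controls, with 20% bacteraemia assumed in cases (Sample size determination).
- Teule identifies 85% of culture-proven bacteraemia (Credibility section).
- Prevalence of invasive bacterial infection of 5.58% in all-severity malaria and 6.4% in severe malaria (Bacterial co-infection section).

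Combining these figures is an assumption, because they come from different study populations.

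- Bacteraemic cases: 105 × 0.20 = 21. Non-bacteraemic cases: 105 − 21 = 84.
- Teule-positive share of malaria admissions: f = 0.85 × prevalence / 0.20.
  - 5.58%: 0.85 × 0.0558 / 0.20 = 0.237.
  - 6.4%: 0.85 × 0.064 / 0.20 = 0.272.
- Bacteraemia in Teule-negative children: p = 0.15 × prevalence / (1 − f).
  - 5.58%: 0.00837 / 0.763 = 1.1%.
  - 6.4%: 0.0096 / 0.728 = 1.3%.
- Expected bacteraemic controls: 50p = 0.55 to 0.66. The chance of none, (1 − p)^50, is 58% to 51%.
- Controls as a share of all non-bacteraemic children: 50 / (84 + 50) = 50 / 134 = 37%.

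**Step 4. What milder controls could do to pooled specificity**

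The article gives no marker specificities, so the values below are assumed and shown as a range. Pooled specificity = (84 × s_case + 50 × s_control) / 134. For example, (84 × 0.60 + 50 × 0.90) / 134 = 95.4 / 134 = 71%.

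| Specificity in non-bacteraemic cases | Controls same as cases | Controls 80% | Controls 90% | Controls 95% |
|---|---|---|---|---|
| 50% | 50% | 61% | 65% | 67% |
| 60% | 60% | 67% | 71% | 73% |
| 70% | 70% | 74% | 77% | 79% |

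The gain is 0.37 times the difference in specificity between controls and non-bacteraemic cases. None of it reflects better discrimination among the at-risk children.

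**The case against.** **A drafting slip.** One section says non-severe and at least five say severe, so the intent may be plain. That is quite possible, and Figure 1 or the full protocol might show it. It does not remove the contradiction from the current text, and it leaves the conflicts over exclusions and temperature untouched. The exclusions conflict is the smallest of the three: those criteria concern azithromycin contraindications and interactions, and controls are not allocated azithromycin.

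**Three mutually incompatible cohorts.** A reader might infer this, but only severe against non-severe is strictly exclusive. The Sample size wording can coincide with the Controls wording if temperature belongs to Teule. A normothermic prostrated child separates those two sections only if a different form of Teule is used for each.

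**Comparison with the controls alone.** A reader of Specific objectives (iii) might infer that bacteraemic children will never be compared with culture-negative cases. The Biomarker and gut barrier function section does not support this. It aims to predict co-infection among at-risk children with severe malaria, and Table 3 schedules a day-0 blood culture without restricting it to cases. A within-case contrast is compatible with the text.

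**The fixed 105:50 ratio.** The Credibility section says of the clinical criteria: "Simple and objective criteria identifying those at risk would be more generalizable outside research centres and would be validated in this study". A reader might infer that Teule sensitivity and specificity will be taken unweighted from the 155 children. No section states that analysis, and the choice of estimator is commonly left to an analysis plan, so no fault is claimed there.

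**Conclusion.** The point holds as an inconsistency in eligibility that affects the second principal objective. Severity is contradicted outright, the scope of the exclusions is contradicted, and the place of temperature in Teule is unsettled.

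The cohort in question supplies about 37% of the expected non-bacteraemic comparators, with about 0.6 bacteraemic children among its 50. That rests on the protocol's 20%, 85% and 5.58–6.4% being combinable. The possible effect on pooled specificity, such as 60% becoming 71%, is an illustration with assumed values. It arises only if the enrolled controls were milder than the cases and the marker responds to severity. The article does not show that either condition was met, so actual inflation is not established.

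The randomised dose comparison and the PKPD analysis use cases only and are untouched.

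**What to change.** 1. Reconcile Target population, Inclusion criteria, Controls, Exclusion criteria, Sample size determination and Treatment allocation to one control definition covering severity, temperature and exclusions. Make the treatment statement consistent with it. This review takes no view on which clinical rule is right.
2. Recruitment is complete (Trial status), so report the severity of the controls actually enrolled. Limit the severe-malaria conclusion under hypothesis 2 and Specific objectives (iii) to children who had severe malaria.
3. Report marker accuracy for culture-positive against culture-negative children within the 105 Teule-positive cases, in line with the sub-study's stated aim. Keep it separate from any estimate that pools in the controls.

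The cost is a text correction and one additional set of results from data already scheduled for collection. The accuracy figures may be less flattering and will be less precise. At an illustrative 60% specificity, the 95% half-width is 1.96 × √(0.6 × 0.4 / 84) = 10.5 percentage points within cases, against 1.96 × √(0.6 × 0.4 / 134) = 8.3 points if all 134 are pooled.

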**Figure 1. f1:**
[figure not shown]
Trial flow. PK, pharmacokinetics; CRP, C-reactive protein. * Days 1-5 inclusive.

### Pragmatic dosing chart

Rather than calculate azithromycin doses based on body weight (which in practice is poorly implemented), the trial will use weight bands (see
Table 1) all using 100mg dispersible tablets, which are more practical and generalizable outside of clinical trials.

**Table 1. T1:** Pragmatic dosing chart for dispersible azithromycin.

	10 mg/kg	100mg tabs	15 mg/kg	100mg tabs	20 mg/kg	100mg tabs
Weight (kg)	Weight x10	Tab size	Weight x15	Tab size	Weight x20	Tab size
5.5 - 6.4	55-64	0.5	82.5-97	1	110-129	1
6.5 - 7.4	65-74	0.5	97.5-112	1	130-149	1.5
7.5 - 8.4	75-84	0.5	112.5-127	1	150-169	1.5
8.5 - 9.4	85-94	1	127.5-142	1.5	170-189	1.5
9.5 - 10.4	95-104	1	142.5-157	1.5	190-209	2
10.5 - 11.4	105-114	1	157.5-172	1.5	210-229	2
11.5 - 12.4	115-124	1	172.5-187	1.5	230-249	2.5
12.5 - 13.4	125-134	1	187.5-202	2	250-269	2.5
13.5 - 14.4	135-144	1.5	202.5-217	2	270-289	2.5
14.5 - 15.4	145-154	1.5	217.5-232	2	290-309	3
15.5 -16.4	155-164	1.5	232.5-247	2.5	310-329	3
16.5 - 17.4	165-174	1.5	247.5-262	2.5	330-349	3.5
17.5 - 18.4	175-184	1.5	262.5-277	2.5	350-369	3.5
18.5 - 19.4	185-194	2	277.5-292	3	370-389	3.5
19.5 - 20.4	195-204	2	292.5-307	3	390-409	4
20.5 - 21.4	205-214	2	307.5-322	3	410-429	4
21.5 - 22.4	215-224	2	322.5-337	3	430-449	4.5
22.5 - 23.4	225-234	2	337.5-352	3.5	450-469	4.5
23.5 - 24.4	235-244	2.5	352.5-367	3.5	470-489	4.5
24.5 - 25.4	245-254	2.5	367.5-382	3.5	490-509	5
25.5 - 26.4	255-264	2.5	382.5-397	4	510-529	5
26.5 - 27.4	265-274	2.5	397.5-412	4	530-549	5.5
27.5 - 28.4	275-284	2.5	412.5-427	4	550-569	5.5
28.5 - 29.4	285-294	3	427.5-442	4.5	570-589	5.5
29.5 - 30.4	295-304	3	442.5-457	4.5	590-609	6
30.5 - 31.4	305-314	3	457.5-472	4.5	610-629	6

This weight-band dosing has been developed based on existing data
^
27
^ and will be validated by the nested PKPD sub-study (as has been done in several HIV trials). Children generally tolerate a wide range of azithromycin doses (5-20mg/kg); however, when given in combination with artesunate, doses of 20mg/kg more commonly resulted in vomiting (versus artemether-lumefantrine)
^
28
^. Based on Monte Carlo simulations, we expect that all dose groups should reach the population reference target (adult) AUC24h of at least 3.4 h*mg/L
^
24
^, although there are no data on absorption in severe malaria, which is characterised by impaired gut function
^
25
^, hence the need for this pilot.

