## Sub-studies

### PKPD study

For PK analysis, model-based sampling strategies will enable the description of both intra- and inter-patient variability. A maximum of 3x 0.2ml samples will be taken from each subject on two occasions between day one to five around meaningful time points to describe the PK throughout a dosing interval plus one sample at follow up on day seven to determine the elimination of azithromycin after end of treatment (a total of seven samples per patient). In the first year we will develop highly sensitive bioanalytical assays using ultra performance liquid chromatography coupled with tandem mass spectrometry (UPLC-MS) for determination of azithromycin in stored microvolumes of plasma (analysis performed at Radboud University, Nijmegen). 

Initially a population PK model will be developed for azithromycin and will investigate possible covariates for its PK. This will be followed by an investigation of the relationship between plasma PK and PD using the developed PK model, known MIC-values since the area under the curve (AUC):MIC ratio is the pharmacodynamic driver for azithromycin
^
16,
30
^ and the treatment outcomes (changes in CRP at day three and microbiologic cure and/or mortality at day seven). Based on Monte Carlo simulations, we expect that all dose groups should reach the population reference target (adult) AUC24h of at least 3.4 h*mg/L
^
24
^, although there are no data on absorption in severe malaria, which is characterised by impaired gut function
^
25
^, hence the need for this pilot. The different doses in 105 children provides variability in exposure so that we identify whether all doses are in the flat part of the exposure-response curve, in which case the lowest dose will be chosen. Other secondary endpoints include mortality at 48 hours, length of hospital stay (days), re-hospitalisation and other adverse events. Quality-control of stored bacterial isolates, non-culture (molecular) assessment of bacterial infection including the determination of MIC to inform PKPD studies will be batch-processed at KWTRP, Kenya.

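### In two of the 26 weight bands of Table 1 the 15 and 20 mg/kg arms receive the same tablet count, so the intention-to-treat 15 v 20 comparison is pulled towards no difference

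*Protocol article*

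**What the plan says.** Under Randomisation procedure: "Children will be randomised (1:1:1) to receive 10, 15 or 20 mg/kg azithromycin (based on weight-bands"). Sample size determination repeats this: "The overall sample size for the trial will be 105 children randomised 1:1:1 to receive 10, 15 or 20mg/kg azithromycin". Treatment allocation likewise describes three doses.

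Under Pragmatic dosing chart: "Rather than calculate azithromycin doses based on body weight (which in practice is poorly implemented), the trial will use weight bands". The dose a child receives is read from Table 1 in that section, in half-tablet steps of a 100 mg tablet. Each row gives, for the 10, 15 and 20 mg/kg arms in turn, the target range in mg and the tablet count. Two rows matter here:

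- "5.5 - 6.4 55-64 0.5 82.5-97 1 110-129 1"
- "8.5 - 9.4 85-94 1 127.5-142 1.5 170-189 1.5"

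The Statistical analysis section compares primary and secondary end points by trial arm, primarily by intention to treat. Its per-protocol set is defined by receipt of five days of azithromycin. The PKPD study section relies on spread in dose: "The different doses in 105 children provides variability in exposure". On power, Sample size determination states: "A formal sample size was not calculated". The article does not mention that two arms coincide in any band.

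**The concern.** Rounding to half tablets normally moves the delivered dose a little within an arm. In these two rows it removes the randomised contrast. A 9 kg child allocated to the 15 mg/kg arm and a 9 kg child allocated to the 20 mg/kg arm receive the same treatment under different labels. This contradicts the description of three randomised doses, and it contradicts the target columns in the same rows.

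Under intention to treat these children are analysed by label. They add variance to the 15 v 20 comparison but no difference in treatment, so the estimate is biased towards zero. The per-protocol set does not help, because it selects on duration and not on amount. The effect is not confined to CRP and microbiological cure. The same article reports more vomiting at 20 mg/kg when given with artesunate, so a by-arm comparison of tolerability between 15 and 20 mg/kg is weakened in the same direction. Both bands are among the four lightest on the chart, and eligibility starts at six months of age.

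**Working it through.** **Inputs.** Tablet counts and band limits for all 26 rows come from Table 1. The 105 children allocated 1:1:1 give 105/3 = 35 per arm. There is no stated power, effect size or weight distribution to reproduce.

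**Step 1: compare counts.** The 15 and 20 mg/kg counts are equal in two rows, 5.5-6.4 kg (1 v 1) and 8.5-9.4 kg (1.5 v 1.5), and in no other. The 10 mg/kg count never equals the 15 or the 20 mg/kg count.

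**Step 2: delivered dose = 100 x tablets / weight.**

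| Band (kg) | Dispensed in both arms | Delivered mg/kg | Target, 15 arm | Target, 20 arm |
|---|---|---|---|---|
| 5.5-6.4 | 100 mg | 100/6.4 = 15.6 to 100/5.5 = 18.2 | 82.5-97 mg | 110-129 mg |
| 8.5-9.4 | 150 mg | 150/9.4 = 16.0 to 150/8.5 = 17.6 | 127.5-142 mg | 170-189 mg |

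In all four cells the dispensed amount lies outside the row's own target: above it for the 15 mg/kg arm, below it for the 20 mg/kg arm.

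**Step 3: the rest of the chart.** At mid-band (5.95 kg, 6.95 kg and so on) the gap between the 15 and 20 mg/kg arms in the other 24 bands runs from 2.6 mg/kg (18.5-19.4 kg) to 8.4 mg/kg (11.5-12.4 kg), against a nominal 5. The 10 v 20 gap is at least 5.6 mg/kg in every band.

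**Step 4: dilution.** Let f be the share of children in the two bands, equal in both arms in expectation because weight is measured before treatment. Suppose the true 15 v 20 difference is D in the other bands and zero here. The expected by-arm difference is (1-f) x D. With unchanged variance, the information about D is that of a sample (1-f)^2 times as large.

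| Assumed f | Children among the 70 in these arms | Difference kept, 1-f | Effective sample kept, (1-f)^2 | Loss |
|---|---|---|---|---|
| 5% | 3.5 | 0.95 | 0.90 | about 10% |
| 2/26 = 7.7% (even weights across bands) | 5.4 | 0.92 | 0.85 | 15% |
| 20% | 14 | 0.80 | 0.64 | 36% |

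**Step 5: what leaving the bands out does.** Excluding them keeps a sample fraction of 1-f with the difference undiluted. At f = 20% that is 0.80 of the information instead of 0.64. At f = 7.7% it is 0.92 instead of 0.85. The restricted analysis is therefore both unbiased for D and more informative about it.

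**The case against.** Five arguments can be made on the other side.

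1. **The dose decision does not rest on arm labels.** The PKPD study section asks whether the doses lie on the flat part of the exposure-response curve, using modelled plasma exposure and MIC. A reader might infer that identical tablet counts bias that judgement towards flatness. The documents do not support this: a child enters the model with the exposure estimated for that child, whichever envelope was opened. What is lost is some spread in dose within two bands. This stands and limits the point to the by-arm analysis.

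2. **The contrast was never powered.** The protocol makes no formal sample size calculation and says trials of this phase are not usually designed to show superiority. A reader might infer that a stated power is damaged; there is none. Still, the Statistical analysis section does plan to compare end points by arm, and that comparison is diluted.

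3. **The arms are openly weight-band strategies.** Intention to treat validly compares those strategies, and it would be wrong to say that the 15 and 20 mg/kg arms are the same treatment overall. They coincide in two bands only. But the labels and target columns promise three doses in every row, and a reader will interpret the result as 15 v 20 mg/kg.

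4. **Other bands offset part of the loss.** With even weights the mid-band 15 v 20 gap averages 4.70 mg/kg over all 26 bands. If the effect is linear in dose, the loss against the nominal design is 1 - (4.70/5)^2, about 12%, not 15%. This is fair, but it depends equally on an assumed weight distribution.

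5. **Recruitment is complete, and sensitivity analyses usually belong in a SAP, which is not shown.** Correcting the chart cannot change doses already given, and insisting on different counts in every band would in effect dictate a dose. Neither is asked for here. The contradiction within the published table stands whatever the SAP contains.

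**Conclusion.** Table 1 contradicts the three-dose design in two of 26 weight bands. There the 15 v 20 allocation changes nothing that the child receives. The intention-to-treat 15 v 20 comparison of end points and adverse events is attenuated by 1-f. The direction is certain if a difference exists. The size is not, because the protocol gives no weight distribution: the 10% to 36% loss of effective sample spans assumed shares of 5% to 20%, and it takes the effect as constant across the other bands.

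One pairwise contrast of three is affected. The harm is to the interpretation of a null 15 v 20 result, not to a stated power and not to the exposure-based dose selection. This should be fixed, and it can be while the data are being analysed, as Trial status reports. It is not a fault that invalidates the trial.

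**What to change.** For the chart: reconcile the 5.5-6.4 kg and 8.5-9.4 kg rows with their own target columns and with the three-dose description before the chart is reused, for example in the Phase III trial. How this is done is for the clinical team; no tablet count is proposed.

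For the current analysis:

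1. Report the number of children in the two bands by arm, so that f is known and not assumed.
2. Report the 15 v 20 contrast for the main end points and adverse events with and without these bands. Weight at randomisation is a baseline value, so the restricted comparison is still randomised.
3. Do not read a null by-arm 15 v 20 result as evidence of a flat dose-response without this check.
4. Use the mg/kg actually dispensed in any dose-response model. Within an arm this varies only with weight, so the model should also adjust for weight.

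The cost is one extra sensitivity analysis that drops a few children (about 5 of the 70 in these arms if weights are even across bands) and a short note beside Table 1. No new data are needed.
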